### Interim analyses {21b}

The corresponding author makes the final decision to terminate the trial, if necessary. This will only happen in case it becomes impossible to clinically attend the participants as, for example, in outbreaks of infectious diseases. The authors will have access to these interim results.

### Methods for additional analyses (e.g., subgroup analyses) {20b}

Not applicable.

### Methods in analysis to handle protocol non-adherence and any statistical methods to handle missing data {20c}

No losses greater them 5% of the sample are expected, and if they happen, pairwise deletion will be used.

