### Criteria for discontinuing or modifying allocated interventions {11b}

If the participant shows signs/symptoms of pulpal involvement and requires other treatment modalities, treatment will be discontinued and the participant data will be excluded from the study. However, they will still be followed up for safety assessment.

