#### Radiographic evaluation

This is one of the primary outcomes of the study. The radiographic examinations will be carried out in the following manner: (1) periapical radiographs will be used as a diagnostic aid; (2) after the incomplete removal of the demineralized dentine and the temporary filling of cavity, a bitewing radiograph it will be taken to allow the analysis of the radiolucent zone (RZ), that is, the amount of demineralized dentine left; (3) immediately, 1 week, and 1, 3, 6 and 12 months, periapical and bitewing radiographs will be taken to analyze the integrity of the periapical area and the eventual changes in the RZ.

To obtain geometric standardization of films, bitewing film holders will be used. The images obtained before and after the treatment will be digitized by a ScanJet 6100 scanner Hewllet-Packard (OR, USA). The images will be stored in maximum-quality JPG format. The Imagelab software (version 2.3, SoftiumSistemas de Informatica, São Paulo, Brazil) will be used to analyze the images (equalize and subtract). Change in the density measurement of the RZ during treatment will be evaluated blind through digital subtraction of radiographic images in relation to the initial exams in the experimental periods (immediately, 1 week, and 1, 3, 6, and 12 months).

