### Sample size {14}

The sample size was calculated based on a previous study in the literature [16, 17] (Fig. 2), considering the expected difference and standard deviation and weighting colony-forming units (CFU) of bacteria. For the statistical calculation, paired samples were considered, with α=5% and an 80% test power. The minimum number in this clinical trial was determined to be 34 teeth per group. Therefore, 40 teeth per group will be recruited to compensate for possible dropouts during the experimental period. G*Power 3.1 was used to perform the calculations (Fig. 3).

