### Plans to promote participant retention and complete follow-up {18b}

As participants will already be in pediatric dentistry treatment, we believe recruitment will be feasible. We believe participants will be present for the follow-ups due to concerns and other possible treatments in the clinic. Phone texts and calls will also be used as visit reminders.

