## Statistical methods

### Statistical methods for primary and secondary outcomes {20a}

The data will be stored in Excel datasets and analyzed statistically by employing different tests and considering a 5% level of significance. Only the researchers involved in the study will have access to the data, even if the study is discontinued. The results will be submitted to the Shapiro-Wilk test to check for normality. In case data distribution is normal, analysis of variance (ANOVA) will be used for both the dependent and independent variables. In case the data distribution is not normal, the Friedman test will be used for the dependent variables, followed by the Wilcoxon test as post hoc. For independent variables, the Kruskal-Wallis test will be used, followed by the Mann-Whitney test as post hoc. Pearson (for normal data) or Spearman (for non-parametric data) correlation coefficients may be calculated to determine correlations among the variables.

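### Pairwise deletion, the plan's only missing-data rule, cannot be applied to the within-tooth omnibus tests named for the repeated radiographic evaluations

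*Protocol article*

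**What the plan says.** The whole missing-data provision is one sentence in {20c}: "No losses greater them 5% of the sample are expected, and if they happen, pairwise deletion will be used". Read literally, it acts only when losses exceed 5% and gives no rule below that; the pronoun could also mean any losses.

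The tests are in {20a}. For normal data, "In case data distribution is normal, analysis of variance (ANOVA) will be used for both the dependent and independent variables". For non-normal data, "the Friedman test will be used for the dependent variables, followed by the Wilcoxon test as post hoc". Arms are compared separately: "For independent variables, the Kruskal-Wallis test will be used, followed by the Mann-Whitney test as post hoc".

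The Outcomes section makes the radiographic and clinical evaluations primary, beside microbiology. Under Radiographic evaluation, "immediately, 1 week, and 1, 3, 6 and 12 months, periapical and bitewing radiographs will be taken": one image at treatment and five return visits.

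Two further passages bear on why data may be missing. On retention, {18b} says "We believe participants will be present for the follow-ups due to concerns and other possible treatments in the clinic", and adds that texts and calls will serve as reminders. For participants with pulpal involvement who need other treatment, {11b} says "treatment will be discontinued and the participant data will be excluded from the study", although safety follow-up continues.

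**The concern.** The stated rule and the stated tests do not fit together. Pairwise deletion drops a case only from those comparisons for which it lacks a value. An omnibus test over several visits is a single comparison that uses all of them, so there is nothing pairwise to do. The analyst must improvise, and the default is to drop the whole tooth, which the plan does not state. Films taken at attended visits are then discarded, and the post hoc tests rest on different teeth from the omnibus test that they follow.

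The second issue is validity. Any deletion rule is unbiased in general only if absence is unrelated to outcome. The plan states no such argument and attaches no sensitivity analysis to the rule.

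**Working it through.** **1. Which of the named tests can carry the rule**

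- Friedman over the visits: no, it needs a complete row per tooth.
- Classical ANOVA over the visits: no, for the same reason.
- Wilcoxon post hoc, two visits at a time: yes, but the teeth differ from pair to pair.
- Correlations: yes.
- Kruskal-Wallis, Mann-Whitney or one-way ANOVA between arms at one visit: the available teeth are used and no complete row is needed.
- CFU before and after removal: both samples come from the treatment session, so later loss does not touch them.

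As a check, a Friedman test was run on simulated data for 40 teeth at 6 times with one empty cell. It returned no statistic. Deleting only that cell left columns of unequal length and the test failed. It ran only under a different missing-value rule, which the plan does not state.

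**2. What the default would cost**

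The plan's own figure first: 5% of the sample is 0.05 × 160 = 8 teeth, or 0.05 × 40 = 2 per group. If the same teeth miss every return visit, 40 − 2 = 38 complete rows remain per group.

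The other extreme is assumed, not stated in the plan: each of the five return visits is missed independently with probability p. Complete rows = 40 × (1 − p)^5.

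- p = 2%: 36.2
- p = 3%: 34.3
- p = 5%: 31.0
- p = 10%: 23.6

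So 5% absence means 38 or 31 usable teeth per group, depending only on the pattern.

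**3. What outcome-related absence would do**

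Observed failure = f·a / (f·a + (1 − f)·b), where f is the true failure rate, a the attendance of failing teeth and b that of sound teeth. All values are assumed.

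- f = 20%, a = 85%, b = 98%: 0.170 / (0.170 + 0.784) = 17.8%. Total loss is 1 − 0.954 = 4.6%, below the 5% trigger.
- f = 20%, a = 98%, b = 80%: 0.196 / (0.196 + 0.640) = 23.4%.
- f = 10%, a = 98%, b = 80%: 0.098 / (0.098 + 0.720) = 12.0%.

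The last two lines, taken as two arms with the same attendance rule, have an observed odds ratio of (0.196/0.640) / (0.098/0.720) = 2.25. The true value is (0.20/0.80) / (0.10/0.90) = 2.25. The rates within each arm are shifted, but the odds ratio between arms is not.

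**The case against.** Much can be said for the plan. Subtraction compares the post-treatment film with each later film in turn, so one missing film naturally removes one contrast, and for those contrasts pairwise deletion has a clear meaning. The section on tests never uses the term repeated-measures ANOVA. A sentence about retention is not a statement of why data will be missing. All of this is fair, but none of it rescues the omnibus test over visits, which {20a} places before the Wilcoxon tests.

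Several stronger readings are tempting, and the document does not support them.

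- *The main comparison of treatments fails.* Between-arm tests at one visit keep every tooth seen at that visit. The text leaves open whether arm and visit would be combined in one classical ANOVA, so this cannot be asserted.
- *Both follow-up outcomes are hit.* Nothing assigns the clinical 0 to 9 code to Friedman or ANOVA. The point is established for the radiographic series only.
- *Complete rows fall below the required 34.* That number was derived from CFU with paired samples, and follow-up loss cannot reduce those. It is no benchmark for the radiographic series.
- *An expected loss of 5% contradicts the 15% margin, (40 − 34)/40.* The sample size section says "40 teeth per group will be recruited to compensate for possible dropouts during the experimental period"; a margin larger than the expected loss is prudent.
- *The plan expects attendance to follow the child's own concerns.* The sentence does not say whose concerns these are or that they relate to the study tooth, and it also names other treatments. A link to outcome is possible, not stated.
- *The treatment contrast will be biased.* With equal attendance behaviour in both arms, the example above leaves the odds ratio unchanged. Different behaviour by arm is conceivable because only the assessors are blinded, but the document gives no evidence of it.

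**Conclusion.** The point stands in a limited form. The only missing-data rule cannot be carried out in the omnibus tests named for within-tooth change, so the radiographic series would be analysed by an unstated complete-case rule. This follows from the tests themselves and needs no assumption about loss. Its size does need one: 31 to 38 complete rows of 40 per group at 5% absence, from independent misses to the same teeth always missing.

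That absence is unrelated to outcome is an assumption for which the plan gives no support. The firmest evidence against it is {11b}, which removes data for a reason tied to the state of the tooth; the retention sentence is weaker, since the concerns may or may not relate to the study tooth. The amount and direction of any bias cannot be derived from the document. The wording should be corrected before analysis; the defect does not undermine the trial as a whole.

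**What to change.** Replace the sentence in {20c} with text to this effect:

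- All randomised teeth are analysed with every observed visit, whatever the proportion lost. The 5% trigger is dropped.
- Change in radiographic density is analysed with a mixed model for repeated measures, with arm, visit and arm by visit as fixed effects and correlation among visits of the same tooth. A tooth with some missed visits then contributes the visits it has. The model is valid if data are missing at random, and this should be stated.
- For restoration failure, best-case and worst-case bounds are reported for children not seen at 12 months, with the codes that count as failure named in advance. With 2 of 40 unseen, the bounds for one arm lie 2/40 = 5 percentage points apart.
- The data exclusion in {11b} and this analysis set must be reconciled. This concerns which data are analysed, not how the child is treated.

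The cost is analysis wording only, with no change to recruitment, visits or treatment. The downside is slightly more analysis work and model assumptions in place of rank tests. The mixed model does not protect against absence that depends on unseen outcomes, and a tooth with no return film still adds nothing on density change.

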### Plans to give access to the full protocol, participant-level data and statistical code {31c}

The final datasets will be available from the corresponding author, at a reasonable request. The authors have the intention of publishing the results, in articles and conferences.

## Oversight and monitoring

### Composition of the coordinating center and trial steering committee {5d}

The authors themselves will coordinate and steer the trial.

### Composition of the data monitoring committee, its role and reporting structure {21a}

Seeing as this is not a study that involves significant safety concerns, risks, or complexity, nor is it a multicenter study of long duration, no data monitoring committee was considered required.

### Adverse event reporting and harms {22}

No major harms are expected, but possible intercorrences, such as tooth pain, will be monitored and recorded. Any additional assistance participants may need, will be provided.

### Frequency and plans for auditing trial conduct {23}

Monitoring will be carried out by sponsor personnel or representatives at the investigation site, monthly.

### Plans for communicating important protocol amendments to relevant parties (e.g. trial participants, ethical committees) {25}

Changes in the protocol will be reported to the Ethics Committee of Faculdade Paulo Picanço and altered in ClinicalTrials.gov.

### Dissemination plans {31a}

After the analysis of the data, volunteers will be invited to a meeting and the results will be shared, in case they wish to attend it. The authors also intend to publish the results.

## Discussion

Studies have shown that the isolated action of aPDT is not completely efficient for the microbial reduction and painful symptoms of patients [18], highlighting the importance of dental professionals in both the treatment and prevention of deep caries-affected dentin of permanent teeth [19]. Procedures using aPDT have also been developed to the treatment of dental caries [3, 4, 19]; however, there are few controlled clinical trials in the literature confirming its efficacy. Papacarie™ is a gel composed of papain and chloramine [8, 9] employed for the partial removal of carious tissue, effective against bacteria due to its properties, but some studies show that the antibacterial action is not so evident. *Bixa orellana* is a Brazilian plant, and its seeds produce one of the most frequently used worldwide dyes, which is called annatto or “urucum” [6, 20]. Its leaves and seeds were reported to have antimicrobial, antifungal, anticonvulsant, analgesic, and anti-inflammatory activities, and showed important activity against Gram-positive and Gram-negative bacteria [21, 22]. The *Bixa orellana* extract proposed with this study could enhance the antimicrobial action through aPDT [6] and improve the effectiveness of conservative treatments using the selective removal of carious tissue and the use of Papacarie™. In addition, there is a tendency for patients to value new treatment technologies, which can increase their satisfaction with this therapy.

## Trial status

This protocol is registered at ClinicalTrials.gov under the number NCT05236205 and it was first posted on 01/21/2022 and last updated on 05/10/2022, https://clinicaltrials.gov/ct2/show/NCT05236205?term=NCT05236205&draw=2&rank=1. Recruitment will take place from 30 May 2022 to 30 April 2023.

## Data Availability

The data sets generated and analyzed during the study will be available from the corresponding author at reasonable request. After the analysis of the data, volunteers will be invited to a meeting and the results will be shared, in case they wish to attend it. The authors also intend to publish the results.

## Abbreviations

aPDT: Antimicrobial photodynamic therapy
CFU: Colony-forming units
LB: Lactobacilli
LED: Light-emitting diode
S: *Streptococcus*
SM: *Streptococcus mutans*
SPIRIT: Standard Protocol Items: Recommendations for Interventional Trials
VM: Viable microorganisms
